# DATA ANALYSIS

**a. Quantitative**

Statistical analyses will be performed using SPSS, version 22. The primary outcome will be reported as numbers and percentages.

Secondary outcome measures will be summarised using mean (SD) for normally distributed data, median (interquartile range) for non-normally distributed data and number (percent for categorical data).

Pre- to post-treatment comparisons will be performed using a paired t-test. Effect size and 95% confidence interval will be reported. The significance level will be set at p<0.05.

In addition, for each of the secondary outcome measures, linear regression will be used to measure changes in secondary variables while controlling for age, cognition, adherence, comorbidities, and ability to implement the MyoMunchee independently.

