# STUDY OUTCOMES

1. **Quantitative**
2. **Primary Outcome**

Feasibility and acceptability of treatment intervention. This will include the number of participants approached versus consented, completed treatment rates, and adherence to the intervention (monitored by care staff with supervision of the intervention, and completion of daily intervention sheets).

1. **Secondary Outcome(s)**

Secondary outcome measures will be collected both pre and post intervention, and are outlined in Table 1.

**Table 1** Secondary outcome measures for collection pre and post intervention

| Outcome Measure | Reference | Outcome | Description |
| --- | --- | --- | --- |
| Oral Health Assessment Tool (OHAT) | [6] | Oral health | Reliable and valid screening tool for use in aged care and with cognitive impairment; Approximately 7-8 minutes to administer; 8 items, Rating scale – 0 = healthy, 1 = changes, 2 = unhealthy; Total score out of 16, The higher the score the worse the oral health; Items that score 1 indicate intervention is required, and items scoring 2 indicate referral to a dental professional is required |
| Timed Water Swallow Test (WST) | [18] | Aspiration risk | Swallow speed is a sensitive indicator for identifying patients at risk of swallow dysfunction; Choking in 100ml WST may be a potential indicator for follow up aspiration; Measures swallow time, number of swallows and observes for signs of choking; Abnormal swallow is defined as a speed below 10ml/s (amount of water divided by elapsed time); Count the number of swallows taken to consume 100mls water; Time taken to consume 100mls water |
| Test of Mastication and Swallowing Solids (TOMASS) | [17] | Mastication ability | Quantitative assessment of solid bolus ingestion; Sensitive in detecting changes in performance ability of mastication; High interrater and test-retest reliability; Count number of bites, number of masticatory cycles per bite, number of swallows per bite; More likely to identify patients with subtle oral phase impairment or bolus transition issues; Normative ranges in older adults: number of bites (male 1.47/female 1.87), time in seconds (male 32.61/female 41.85), total number of swallows (male 3.61/female 3.5), masticatory cycle (male 37.6/female 41.65) |

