| Mann Assessment of Swallowing Ability (MASA) | [24] | Identify swallowing disorders | Screening bedside tool to identify eating and swallow disorders in stroke and other diseases; Used to quantify aspiration risk; 24 clinical items; 4 components of the assessment include, general patient examination, oral preparation, oral phase, and the pharyngeal phase; 5-10 point rating scale; score out of /200, >178 = normal, 168-177 = mild, 139-167 = moderate, <138 = severe; risk of aspiration is defined on a sum of the 4 scores/categories, >170 = normal, 149-169 = mild, 141-148 = moderate, <140 = severe |
| Functional Oral Intake Scale (FOIS) | [8] | Functionality | 7 point ordinal scale; Functional level of oral intake of food and liquid; Interrater reliability high and sensitive to changes; Levels 1-3 relate to non-oral feeding; Levels 4-7 relate to varying degrees of oral feeding; All levels focus on what is/not consumed orally |
| Eating Assessment Tool (EAT-10) | [4] | Self-perceived symptoms | Screen self-perceived oropharyngeal dysphagia symptoms; Scores range from 0-40; Scores >3 are indicative of dysphagia; 10 questions rated on a 5 point scale, 0 = no problem, 4 = severe problem; Scores >15 indicative of aspiration risk; An elevated EAT-10 score indicates a higher self-perception of dysphagia |
| Mini Mental State Examination (MMSE) | [26] | Cognitive function | Widely used screening test of mental function; Evaluates cognitive impairment in older adults; 10 minutes to complete; normal = 30-25, mild = 24-21, moderate = 21-10, severe = 9-0 |

1. **Qualitative**
2. Administer Care Staff Acceptability Questionnaire to those assisting with the intervention/observing the use of the myofunctional device to rate the ease of use and cleaning of the device, the impact on workload, and perceived acceptance by residents.

Administer a Resident Acceptability Survey to all enrolled residents, regarding ease of use, comfort with use, and if there were perceived changes to oral health or swallowing following the use of the device. Assistance in reading the survey to those residents with visual impairment, aphasia, and cognitive and intellectual impairment will be provided by the care staff.

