# STUDY PROCEDURES

1. **Recruitment of participants**

All residents and care staff who meet the selection criteria will be eligible to participate in this study. They will be identified by the Nursing Unit Managers (NUM) and the speech pathologist/s at Maroba Aged Care and provided with an information flyer (Resident Information Flyer, Appendix O. Care Staff Information Flyer, Appendix P). The residents/families of residents/care staff will be provided with a participant information statement (Residents, Appendix Q. Care staff, Appendix R) regarding the study, and then followed up by the NUM/speech pathologist for interest in study participation. There will be an opportunity for residents, family of residents, and care staff to ask questions before and after consenting to participation. Questions regarding the study can be directed by the staff at Maroba Aged care to the Principal Investigator. Residents/family of residents/care staff will be required to sign and provide written consent for participation (Residents, Appendix S. Care staff, Appendix T). Consideration and return of consent for participation in the study will be 7 days after initial contact.

Explanation will be provided to residents/family of residents that their usual oral health care and dysphagia treatment will not vary with or without participation in this study. Further to this, a statement will be provided to participants that based on the results of the pilot study, the larger clinical trial may not be performed.

This research will involve the use of information without personal identifiers and it will be obtained from individuals or gathered from medical files by care staff appointed by Maroba Aged Care. The existing data information seen in section 9d. will be collected for each consented resident.

As this is a feasibility study utilising a myofunctional device not previously trialled in this setting, all consented residents will receive the treatment intervention to better understand acceptability of the device and feasibility of completing a larger trial. No randomisation of participants will occur. The number of participants that will be aimed for recruitment – up to 50 residents and 10 staff. This is based on the available recruitment pool, and the number of residents who may not give consent. Because this is a feasibility study this does not require sample size base.

The period of time for expected time to recruit participants is four weeks.

1. **Study procedures**

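### One unrestricted paired t-test is fixed for every pre-post comparison, although the plan expects non-normal and categorical secondary outcomes; the test and interval should follow the data type

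*Protocol*

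**What the plan says.** Protocol, DATA ANALYSIS, a. Quantitative, sets out how secondary outcomes are described. Normal data get a mean and SD, and the rest get "median (interquartile range) for non-normally distributed data and number (percent for categorical data"). The comparison rule that follows draws no such distinction: "Pre- to post-treatment comparisons will be performed using a paired t-test". It continues "Effect size and 95% confidence interval will be reported" and "The significance level will be set at p<0.05". No alternative test, transformation or condition on normality is given. The next paragraph is equally general: "for each of the secondary outcome measures, linear regression will be used to measure changes in secondary variables".

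Table 1 in STUDY OUTCOMES shows what these rules apply to:

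- FOIS is a "7 point ordinal scale".
- The water swallow test "Measures swallow time, number of swallows and observes for signs of choking".
- TOMASS yields counts of bites, chewing cycles and swallows. The quoted norms include a time, about 1.5 to 1.9 bites and about 3.5 swallows.
- OHAT (out of 16), EAT-10 (0 to 40), MASA (out of 200) and MMSE (up to 30) are bounded scores.

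The recruitment target in STUDY PROCEDURES is "up to 50 residents and 10 staff", with no sample-size basis. The primary outcome is feasibility, reported as numbers and percentages. The Abstract says that efficacy will be judged on the secondary measures.

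**The concern.** Within one section the plan accepts that some secondary outcomes will not be normal and some will be categorical, and then applies a single mean-based method to all of them. This is a rule the Protocol states, not a detail left for a later document.

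Two things are at stake. First, an outcome described by its median or by percentages would carry a p-value and 95% interval for a mean change, so the description and the inference would answer different questions. Second, where few residents change, a t-test can fall below 0.05 on a table that an exact test would not call significant. Because the Abstract and the aim use efficacy language and the results are to guide a randomised trial, such a result could be given more weight than it deserves.

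**Working it through.** The Protocol states no power, SD, change rate or overall error rate, so there is no figure of its own to reproduce. Two-sided tests are assumed, in line with the 95% interval. All distributions below are assumptions.

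**1. Sparse change, n = 50.** Suppose k residents improve by one step, none worsen and the rest are unchanged. This covers a one-level FOIS gain or a yes/no outcome.

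- Paired t: mean = k/n; variance = (k/n)(1 − k/n)·n/(n − 1); t = mean/√(variance/n) on 49 df.
- Exact sign test, identical to exact McNemar here: p = 2 × 0.5^k.

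For k = 5: mean 0.10, variance 0.10 × 0.90 × 50/49 = 0.0918, SE = √(0.0918/50) = 0.0429, t = 2.33, p = 0.024, 95% CI 0.014 to 0.186. Exact p = 2/32 = 0.0625. The median change is 0, since 45 of the 50 changes are 0, yet the interval for the mean excludes 0.

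For 7 improved and 1 worsened, the exact p is 2 × (8 + 1)/256 = 0.070.

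| Improve v worsen (n = 50) | Paired t p | Exact p |
|---|---|---|
| 4 v 0 | 0.044 | 0.125 |
| 5 v 0 | 0.024 | 0.0625 |
| 7 v 1 | 0.032 | 0.070 |

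**2. Does the t-test have the wrong error rate in general?** Two-sided type I error of the paired t-test at 0.05, 20,000 simulated trials per cell:

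| Assumed outcome under no effect | n = 50 | n = 10 |
|---|---|---|
| Overdispersed counts, mean 3.5 | 0.050 | 0.047 |
| Lognormal times, same distribution before and after | 0.041 | 0.033 |
| Ordinal, 20% change by one level, symmetric | 0.043 | 0.012 |
| Yes/no, 10% discordant, symmetric | 0.047 | 0.001 |
| Strongly skewed change (centred lognormal, mean 0) | 0.10 | 0.16 |

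The test is near nominal or conservative except where the change itself is strongly skewed. In the yes/no case at n = 10, no resident changes in about 0.9^10 = 35% of trials, and the t statistic is then undefined.

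**3. Would any rank test help with FOIS?** If all k changes are one level in the same direction, the tie-corrected large-sample signed-rank statistic is z = √k. For k = 5, z = 2.236 and p = 0.025; for k = 4, z = 2 and p = 0.046. These nearly equal the t-test values, so only an exact version alters the conclusion. A Hodges-Lehmann interval on the k = 5 data, with zeros kept, is 0 to 0 and tells the reader nothing.

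**4. Number of tests.** One outcome per instrument gives 7. Counting the listed components (OHAT 1, water swallow 3, TOMASS 3, MASA 1, FOIS 1, EAT-10 1, MMSE 1) gives 11, TOMASS time makes 12 and swallow speed 13. For independent tests, the chance of at least one false positive is 1 − 0.95^m:

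- m = 7: 0.30
- m = 11: 0.43
- m = 12: 0.46
- m = 13: 0.49

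With a common correlation of 0.5, simulation gives about 0.23 for 7 and 0.32 for 12.

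**The case against.** The strongest reply is that the paired t-test depends on the distribution of the change, not of the raw score, and is robust at the planned size. Most of step 2 supports this. A reader might infer that p-values and intervals will be wrong for several outcomes; the documents do not support that. They give no distribution for any change score, and neither skewed swallow times nor a mostly static FOIS is stated. Part of the gap in step 1 is also conservatism of the exact test: with 10% of 50 residents changing symmetrically, the sign test's simulated error is about 0.01. The gap alone therefore does not show that the t-test is invalid.

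Two further points stand. Table 1 gives no coding for choking and defines no dichotomised dysphagia outcome, so a yes/no endpoint is an inference, though the summary rule does foresee categorical data. A reader might also take the number of tests as making individual results wrong. It does not: multiplicity is a separate matter, and a rule for it is commonly left to an SAP.

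The reassurance has limits. Fifty is a ceiling, and consent and completion are themselves under study, so the number of completed pairs may be well below 50. Nor does robustness reconcile a median or percent summary with a mean-based test.

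**Conclusion.** The point holds as an internal mismatch with limited numerical consequences. The plan foresees three data types and fixes a comparison suited to one. It can mislead in three situations: sparse ordinal or yes/no changes (0.024 against 0.0625 for 5 v 0 of 50), strongly skewed changes (simulated error 0.10 at n = 50 and 0.16 at n = 10), and a small completed sample, where sparse outcomes make the test very conservative or undefined. With close to 50 pairs, most other outcomes are handled adequately. These sizes rest on assumed distributions and change rates, and the yes/no case also on an assumed coding.

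The number of outcomes supports labelling the p-values exploratory and nothing stronger. The documents do not compel the choice of particular key secondary outcomes; that would be a design preference.

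**What to change.** Replace the single-test sentence with a rule by data type:

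- **Approximately normal change scores:** keep the paired t-test with its 95% CI.
- **Skewed times and counts:** use an exact signed-rank test with a matching interval, or analyse times on the log scale.
- **FOIS:** report the proportions improved and worsened with exact CIs, and an exact sign test.
- **Any outcome coded yes/no, such as choking:** state the coding, and use exact McNemar with a CI for the paired difference.

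Say explicitly that the versions are exact, since the large-sample signed-rank test would leave the FOIS problem in place. Label all secondary p-values exploratory, in keeping with a feasibility primary outcome.

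The cost is analysis wording, with no extra data collection, and slightly less power for some outcomes. For example, the sign test cannot fall below 0.05 until six residents move, all in the same direction (2 × 0.5^6 = 0.031).

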**b. Qualitative**

Qualitative content analysis as described by Graneheim and Lundman (2004) will be used to analyse participants' responses on both the resident survey and care staff post intervention questionnaire.

**c. De-identification**

All residents who are consented to the study where biographical data is collected will be assigned a resident ID number. The participants identity will not be identifiable to those outside of the research team.

# DATA HANDLING AND RECORD KEEPING

1. **Data Collection and Management Responsibilities**

The study will adhere to The Australian Code for the Responsible Conduct of Research (2018) as well as the University of Newcastle Data management policy (2017).

Data collection and management is the responsibility of the research team from the University of Newcastle and Maroba Aged Care, under the supervision of the Principal Investigator. The care staff are responsible for ensuring the accuracy, completeness, legibility, and timeliness of the data collection during the intervention.

The data and biographical information will be collected in paper form by an employee appointed by Maroba Aged Care. The data will be deidentified using a code and then provided to the research team. The data will be transferred by the research team while onsite at Maroba Aged Care to a University of Newcastle supported data storage platform (OneDrive/Teams) that is password protected and accessed for analysis by the research team.

1. **Study Records Retention**

The Principal Investigator will maintain all records pertaining to this study and will be retained as per the [State Records Act 1998](https://policies.newcastle.edu.au/directory-summary.php?legislation=26) and the University of Newcastle Data Management Policy (2017) for 5 years at the University of Newcastle.

Research data and primary materials will be retained for sufficient time to allow them to be referenced by other researchers and interested parties. In the event that results from research are challenged, all associated research data and materials must be retained until the matter is resolved.

Research data and primary materials will be disposed of in accordance with the relevant legislated minimum retention period of 5 years and with the consent of the research team as per the Australian Code for the Responsible Conduct of Research (2018).

# PUBLICATION & INTELLECTUAL PROPERTY

1. **Dissemination of results to participants**

Participants on signing the consent form for participation can elect to be notified of the results of the study, and the format this is received (electronic, hard copy of the results). This will be outline further in the Participant Information Sheet.

# ETHICAL CONSIDERATIONS

All eligible and consented participants will be informed of the potential risks and proposed benefits of the study procedures, the priority of the participants’ interests over those of science or of society.

The Myofunctional Device (MyoMunchee
[figure not shown]
) has been approved by the Australian Government Department of Health (2019), Therapeutic Goods Administration as a medical device class 1 (low risk device), with intended purpose to exercise the jaw and surrounding muscles, as well as other conditions treated by oral motor therapy. The myofunctional device (MyoMunchee
[figure not shown]
) is ISO 13485 certified by the Standard for Quality Management System for design and manufacturing of medical devices, and is made of non-toxic medical grade silicone.

1. **Vulnerable populations**

This study will involve vulnerable populations, including the elderly and those with chronic health conditions (including cognitive difficulties such as dementia). Informed consent will be obtained from residents/family members of residents if resident unable to provide consent/care staff to take part in this research. Residents/family members of residents/care staff will be required to read and understand the information (Participant Information Statement (PIS)) provided by the research team they need to make an informed decision about their voluntary participation. There will be allowances made for those who cannot read but would like to participate and the PIS can be read to them. Participants/family members of participants who consent to the intervention are permitted to change their mind and withdraw from participation at any time during the study.

1. **Confidentiality**

Confidentiality of all records is guaranteed and no information by which a person can be identified will be released and only anonymous data will be published. Participants will be assigned a pseudonym for the purposes of presentation/further dissemination of the research in order to protect their privacy and confidentiality. All files will be password protected and only accessible by the research team at the University of Newcastle.

1. **Ethical Review**

The study will be conducted in full conformance with principles of the National Statement on Ethical Conduct in Human Research (NHMRC, 2007), Australian Code for the Responsible Conduct of Research (2007) and within the laws and regulations Australia.

Ethical approval will be sought from the following:

- University of Newcastle Ethics committee
- Maroba Aged Care

# OUTCOMES AND SIGNIFICANCE

The outcomes from this study of feasibility and efficacy of test procedures for the use of a myofunctional device in improving in oral health and dysphagia in an aged care population, will further guide the design of a randomized control trial.

